### Sites and investigators

Since the type of site is a variable that might influence the management of patients with BD and the profile of patients attending each type of site may be different, it was necessary to select different types of sites to obtain a representative sample. Generally, patients with BD are seen in mental health centres, clinics, private settings, hospitals or specialised units. Since this distribution varies from one country to another, the study centre selection process had to be adapted locally.

Selection of participating sites was based on the percentage of patients that attend different types of sites in each country, thus ensuring that patients attending one specific site type are not over-represented in the study sample (Table 1). These percentages were obtained either from the literature or from expert panels from each participating country.

**Table 1 T1:** Patient recruitment by country and type of study centre

Country	Site type	Patients per site type (%)	Total patients enrolled
Austria	University hospital	16	20
	Private practice	65	81
	General hospital	19	24

Belgium	Clinics	46	190
	Private practice	31	129
	General practitioner	23	95

Brazil	Public hospital	88	146
	University hospital	12	20

France	Hospital/clinics	49	247
	Private practice	51	260

Germany	University hospital	27	59
	Community hospital	21	46
	Private practice	52	114

Portugal	Hospital	24	123
	Private practice	57	295
	Mental health clinic	19	98

Romania	Ambulatory	37	68
	Hospitals	63	115

Turkey	Private practice	39	151
	University hospital	42	162
	State hospital	18	70

Ukraine	Mental health clinic	90	199
	Private practice	10	22

Venezuela	Private practice	33	76
	Public hospital	67	155

The number of participating investigators is sufficient to ensure: 1) that there is a representative sample of the whole psychiatrist population in each country; and 2) inclusion of a sufficient number of patients to provide the required sample size calculated for the study. No other criteria were applied to selection and inclusion of investigators, in order to avoid any selection bias.

Approximately 250 study centres in 10 countries are participating in the study. Based on the criteria described above, target percentages of patients recruited by each type of study centre were devised to reflect management practices in each of the participating countries (Table 1). The study data will be able to provide a global perspective on comparisons between public *vs *private care, academic hospital *vs *standard hospital care, and hospital *vs *non-hospital care.

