One of the key challenges in ensuring that a new study produces meaningful data is to avoid any selection bias in recruitment of both investigators and patients. This can be achieved by having as few exclusion criteria as possible. A further challenge is to recruit patients without contravening the diverse range of laws, which vary within and between countries, covering privacy relating to the acquisition and use of medical data. A recent study in another area of medicine has attempted to avoid investigator bias in patient selection by engaging a third party to manage patient selection and recruitment [11]. In that study, patients were able to opt out without consulting their physician.

In view of the above, the overall objectives of the Wide AmbispectiVE study of the clinical management and burden of Bipolar Disorder (WAVE-bd) study are: to provide accurate and reliable information on the management of patients with BD in conditions representative of everyday clinical practice; to determine the clinical outcomes of such management and the use of resources in relation to the disease; and to establish the factors associated with different management patterns and clinical and functional outcomes.

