### Patient population

Each investigator identified all patients with at least one mood event in the 12 months prior to the beginning of the study (Time 0), except for those whose index mood event occurred in the 3 months before the study start.

The aim of the study is to achieve systematic inclusion of patients, therefore, where possible, every eligible patient identified at each of the study centres was invited to participate. The main exceptions were at those sites that saw a high number of eligible patients during the recruitment period. At these sites, investigators were allowed to recruit a representative sample using an electronic application, which makes selections by simple randomisation, in order to avoid any type of selection bias.

Patients aged ≥ 18 years, with a diagnosis of BD type I or II (DSM-IV-TR [1]) in any phase of the disorder and who had at least one mood event (depression, mania, hypomania or mixed) according to the DSM-IV-TR definitions during the 12 months prior to the beginning of the study were eligible for recruitment, except for those starting the index mood event less than 3 months before Time 0, subject to their providing informed consent. However, those patients starting the index mood event more than 3-months before Time 0 were eligible even if the index event was not resolved, or if the index event had resolved and they subsequently initiated another event.

Patients not eligible to participate in the study were those participating in an interventional clinical study and any patients unable to complete Patient Reported Outcomes questionnaires.

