All of the studies described above were based on low rates of recruitment from the eligible population. A total of 3188 randomly selected patients were invited to participate in the WAVE-bd study. Of these, 2965 (93%) accepted the invitation to participate and provided written informed consent. The other 7% of patients screened declined to participate and will not be included in the analysis. The systematic approach to inclusion of patients in the WAVE-bd study and stratification by type of study centre to reflect local practice, combined with the 93% patient acceptance rate, leads us to believe that the study population avoids selection bias and is truly representative of the overall global population with unstable BD. Consequently, the investigators believe that the study promises to provide psychiatrists with reliable and up-to-date information about the factors associated with different management patterns of BD on a global scale.

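### The number of investigators cannot ensure that each country's psychiatrists are represented, and neither the site-type stratification nor the patient-level safeguards fill that gap

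*Protocol article*

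**What the plan says.** All references are to the protocol article.

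- **Sites and investigators, number.** The claim is: "The number of participating investigators is sufficient to ensure: 1) that there is a representative sample of the whole psychiatrist population in each country". The same section adds: "No other criteria were applied to selection and inclusion of investigators, in order to avoid any selection bias".
- **Sites and investigators, site type.** "Selection of participating sites was based on the percentage of patients that attend different types of sites in each country". On their source: "These percentages were obtained either from the literature or from expert panels from each participating country". Table 1 lists percentages and patients enrolled by country and site type.
- **Sites and investigators, size.** "Approximately 250 study centres in 10 countries are participating in the study". No count of investigators and no national total of psychiatrists is given.
- **Background.** Selection bias among both investigators and patients is named as a key challenge, and the remedy offered is: "This can be achieved by having as few exclusion criteria as possible".
- **Patient population.** Eligible patients were invited where possible. At sites with many eligible patients, "investigators were allowed to recruit a representative sample using an electronic application, which makes selections by simple randomisation".
- **Discussion and conclusions.** Of 3188 patients invited: "Of these, 2965 (93%) accepted the invitation to participate and provided written informed consent". The section says that random selection from each investigator's recorded patients, with the large sample, ensures representativeness. It then expresses the belief that the study population is free of selection bias and represents the global population with unstable disease.

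**The concern.** Whether a set of psychiatrists represents a country's psychiatrists depends on how they were identified and on who agreed to take part. The article offers their number as the reason, together with the absence of criteria beyond site type. Neither controls which psychiatrists take part.

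This matters because a main objective is to describe how bipolar disorder is managed in everyday practice and to compare countries. Treatment choice and visit scheduling lie largely with the psychiatrist, so the psychiatrist is a source of variation in the very thing being described. If participating psychiatrists manage patients differently from their peers, sampling patients at random within their practices leaves that difference in place. A reader who accepts the stated guarantee would take country percentages as national practice when they describe participating centres.

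**Working it through.** **1. What each safeguard covers**

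| Safeguard | Where described | Acts on | Makes psychiatrists within a site type representative? |
|---|---|---|---|
| Stratification by site type | Sites and investigators, Table 1 | Mix of patients across settings | No |
| No further selection criteria | Sites and investigators | Formal eligibility of investigators | No; it does not determine who takes part |
| Number of investigators | Sites and investigators | Random error | No |
| Simple random draw | Patient population | Patients, at busy sites | No; conditional on the site |
| 93% acceptance | Discussion and conclusions | Patients: 2965/3188 = 0.930 | No |

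No row describes a probability selection or an acceptance rate for investigators.

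**2. The population named.** Belgium's Table 1 entries are 190 + 129 + 95 = 414 patients. General practitioners account for 95/414 = 22.9%, listed as 23%. For that country the investigators do not correspond to a psychiatrist population.

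**3. The only sample-size figure in the article.** Sample size gives 370 patients per country for an expected proportion p = 0.35 and precision d = 0.05 with a 95% interval.

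- Plain formula: n = 1.96² × p(1 − p)/d² = 3.8416 × 0.2275/0.0025 = 349.6, so 350.
- With a continuity correction: n + 1/d = 349.6 + 20 = 369.6, so 370. This reproduces the stated figure.

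The calculation concerns precision for a patient-level proportion. It has no term for the selection of investigators, and no corresponding calculation is given for them.

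**4. Why number does not help: an illustration with an assumed bias.** Suppose patients of participating psychiatrists have a true proportion of 0.40 where the country's is 0.35. The 0.05 difference is assumed; nothing in the article supplies it.

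- n = 370: SE = √(0.40 × 0.60/370) = 0.0255, half-width 0.050. The 95% interval covers 0.35 about 50% of the time.
- n = 2965: SE = √(0.24/2965) = 0.0090, half-width 0.018. It covers 0.35 less than 0.1% of the time.

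A larger sample narrows the interval around the wrong value.

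**5. Random error from few centres, a separate matter from bias.** The mean is 250/10 = 25 centres per country. The article gives no counts by country. Allocating in proportion to enrolment (assumption) gives Austria 250 × 125/2965 = 10.5, Brazil 250 × 166/2965 = 14.0 and Romania 250 × 183/2965 = 15.4.

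- *All-or-none worst case.* Assume one investigator per centre, who either always or never uses a practice, with prevalence 0.5. The half-width 1.96 × √(0.25/m) is 0.310, 0.196 and 0.155 for m = 10, 25 and 40.
- *A less extreme case, Austria.* With 2965/250 = 11.86 patients per centre and an assumed intracluster correlation of 0.1, the design effect is 1 + 10.86 × 0.1 = 2.09. The half-width is 1.96 × √(0.25/125) × √2.09 = 0.088 × 1.44 = 0.127, about 13 points.

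Both results describe random error under random sampling. Neither measures selection bias.

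**The case against.** The strongest reply is that the sentence should be read with what precedes it. Sites were stratified by type with country-specific percentages, so the claim may mean only that, within that stratification, there are enough investigators. The document is a condensed article, and sampling frames and invitation counts commonly sit in the full protocol. The stated aim under Study population is a representative patient population, which is supported by systematic invitation, random draws at busy sites and 93% acceptance. The final conclusion is worded as a belief, enrolment is complete, and no planned analysis uses the claim.

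Much of this stands. The stratification is a real strength. The article's silence on how investigators were approached is not evidence that no random draw was made. A reader might infer that centres volunteered or that psychiatrists selected themselves; the article says neither. The Background remark on few exclusion criteria covers investigators as well as patients, so it should not be read as a rule for patients only.

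The reply does not rescue the sentence. The article does more than omit detail: it gives a guarantee and a reason for it, and the reason is invalid. Balance across settings leaves open which psychiatrists take part within each setting. The patient-level safeguards apply only after a site has joined.

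**Conclusion.** The point holds as an unsupported claim of representativeness. Neither the number of investigators nor the site-type stratification makes psychiatrists within a site type representative of their country. The protections that are described beyond stratification apply to patients, and in Belgium the sites extend past psychiatry.

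The size of any selection bias cannot be computed from the article. It would be tempting to quote 31, 20 or 15 points as its size. Those figures are an all-or-none worst case for random error, resting on one investigator per centre and a prevalence of one half; for Austria the figure falls to about 13 points at an assumed intracluster correlation of 0.1. A reader might also infer that the country results are biased. The article does not show that either. What follows is narrower: country results describe patients of participating centres, balanced by site type, and extension to national practice is a judgement that the described design does not guarantee.

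**What to change.** 1. In Sites and investigators, delete the first numbered claim, on a representative sample of psychiatrists.
2. State that country results describe patients of participating centres, balanced by site type.
3. In Discussion and conclusions, limit both representativeness statements in the same way: the one that says random selection and sample size ensure it, and the closing one on freedom from selection bias.
4. Report management results with the between-centre spread within country beside the patient-level percentage.
5. Where records exist, report centres approached and accepting by country and site type. The article mentions no such records, so this step is conditional.

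The cost is a less favourable claim and a little more analysis. No new patient data are needed and the design does not change.

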### Patient population

Each investigator identified all patients with at least one mood event in the 12 months prior to the beginning of the study (Time 0), except for those whose index mood event occurred in the 3 months before the study start.

The aim of the study is to achieve systematic inclusion of patients, therefore, where possible, every eligible patient identified at each of the study centres was invited to participate. The main exceptions were at those sites that saw a high number of eligible patients during the recruitment period. At these sites, investigators were allowed to recruit a representative sample using an electronic application, which makes selections by simple randomisation, in order to avoid any type of selection bias.

Patients aged ≥ 18 years, with a diagnosis of BD type I or II (DSM-IV-TR [1]) in any phase of the disorder and who had at least one mood event (depression, mania, hypomania or mixed) according to the DSM-IV-TR definitions during the 12 months prior to the beginning of the study were eligible for recruitment, except for those starting the index mood event less than 3 months before Time 0, subject to their providing informed consent. However, those patients starting the index mood event more than 3-months before Time 0 were eligible even if the index event was not resolved, or if the index event had resolved and they subsequently initiated another event.

Patients not eligible to participate in the study were those participating in an interventional clinical study and any patients unable to complete Patient Reported Outcomes questionnaires.

### Measurements

The WAVE-bd study aims to provide a wide-ranging picture of BD management practices, and impact on patients, caregivers and healthcare resource use across a range of countries. For this reason, several measuring instruments are being employed to maximise the types of data collected. All instruments have been validated before the study start, including linguistic validation where needed. In all cases, the scales were also psychometrically validated, at least in the original language. Information regarding demographics (sex, race, age, educational level, professional status, degree of disability, degree of independence or co-residence), alcohol and other substance abuse, medical history, disease characteristics (date of first diagnosis, type of BD, family history of psychiatric diseases, episodes during the last 12 months, presence of psychotic symptoms, hospital admissions, and suicide attempts), treatments received (drug, schedule and dose, and whether the patient received psychologist or group therapy), healthcare resources use, and clinical outcomes will be collected throughout the study (Table 2).

**Table 2 T2:** Study plan and assessments

Time	First visit*	Each other visit	Last visit
Site information	X		
Patient demographics	X		
Medical history	X		
Disease characteristics	X		
Treatment information	X	X	X
Healthcare resources consumption	X	X	X
Clinical outcomes	X	X	X
Adherence to treatment	X	X	X
Quality of life	X	X	X
Functioning	X	X	X
Caregiver demographics	X**		
Caregiver burden	X**		

* First visit: the visit when the patient signs the informed consent form.

** If the caregiver does not attend this visit, the information will be collected at the next visit that the caregiver attends. This information will be collected (if the caregiver consents) only once during the study period for each caregiver. In the event that the caregiver does not attend any visits, this information will not be collected.

An electronic adaptation of the National Institute of Mental Health prospective Life Chart Methodology (NIMH-LCM™) will be used specifically for assessing clinical outcomes during both the retrospective and the prospective phases of the study. It allows the daily assessment of mood and episode severity, based on the degree of mood-associated functional impairment. The NIMH-LCM provides a visual method of tracking the patient's mood at each visit. Each form covers a 1-month period, and clinicians rate both mania and depression on the chart, list the medications taken by the patient during the month, and record any other non-mood symptoms (prospective phase only), if applicable [12].

During the prospective phase of the study the following assessments will be performed to evaluate clinical outcomes, adherence to treatment, quality of life, patient functioning and caregiver burden:

*CGI-BP scale: *this is an adaptation of the Clinical Global Impressions (CGI) scale designed to assess global illness severity and change in patients with BD. It contains nine items [13].

*DAI-10 scale: *the Drug Attitude Inventory (DAI) is a self-applied scale to measure subjective responses to medication. This instrument reveals whether the patient is satisfied with their treatment and evaluates their understanding of how the treatment is affecting them. The reduced version 'DAI-10' has ten highly specific items of subjective experience. These are based on the true recorded and transcribed accounts of patients, and response options are true/false only. These items were selected for their capacity to discriminate between medication adherence grades in a way that can be analysed statistically. Although the DAI is specific for schizophrenia, it has also been used to investigate treatment adherence in patients with BD [14].

*MPR: *the Medication Possession Ratio (MPR), first described by Sclar *et al *[15], is a formula used to determine adherence measured from the first to the last prescription, with the denominator being the duration from index to the exhaustion of the last prescription and the numerator being the days supplied over that period from first to last prescription. The MPR will also be used for the retrospective phase of the study.

*EQ-5D questionnaire: *this is a standardised instrument used to measure health outcomes [16]. It is applicable to a wide range of health conditions and treatments, and it provides a simple descriptive profile and a single index value for health status. The respondent is asked to indicate their health state by marking the box against the most appropriate statement in each of the five dimensions. This decision results in a one-digit number expressing the level selected for each dimension. The digits for five dimensions can be combined in a five-digit number describing the respondent's health state. It should be noted that the numerals 1-3 have no arithmetic properties and should not be used as a cardinal score.

*FAST scale: *the Functioning Assessment Short Test (FAST) is a brief instrument designed to assess the main functional problems experienced by psychiatric patients, particularly bipolar patients. It comprises 24 items that assess impairment or disability in six specific function domains: autonomy, occupational functioning, cognitive functioning, financial issues, interpersonal relationships and leisure time. The total score across all domains will be measured [17].

*BAS: *The Burden Assessment Scale *(*BAS) was developed by Reinhard and Horwitz [18] and will be assessed once during the study. The questionnaire contains 19 items that capture both objective and subjective consequences of providing ongoing care to the seriously mentally ill. The scale distinguishes burden from the measurement of the ill relative's disruptive behaviours and the family's care-giving activities. These are viewed as predictors rather than aspects of burden [18].

### Statistical analyses

Descriptive statistics will include frequency tables (n, mean, median, standard deviation, minimum and maximum for continuous variables and n, frequency and percentage for categorical values). For the population estimation of the variables, the two-sided 95% confidence interval will be obtained.

In order to assess the association of patient characteristics (including functioning and quality of life status) and clinical management (an independent variable) with clinical outcome variables (clinical evolution, mood events, treatment-related events, suicide attempts, variation in scales), logistic and general linear models have been planned. Interest will focus separately on the management differences between the models or groups of models. Model-based point estimates of odds ratios and corresponding 95% confidence intervals will be reported. P-values will be reported for the comparison between different treatments. Since visit-by-visit information from the study index event is being collected, there will be data on patient status during the whole study period. Therefore, it will be possible to analyse data, relative to the time of mood event initiation.

Cox models for survival outcomes, and mixed models for longitudinal data using country as indicator variables, adjusted for age and gender, have been planned in order to investigate differences in clinical outcomes and related factors between countries. A descriptive analysis has been planned to assess factors related to consumption of healthcare resources and caregiver burden, according to caregiver-reported outcomes.

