The emerging picture of the course of BD is quite heterogeneous and includes slow or incomplete recovery from acute episodes, continued risk of recurrences, and sustained morbidity over time, even with continuous long-term use of current treatments. Recovery from an acute episode of mania, even if treatment is established very early in the course of the disorder, may require 3-6 months and thus may no longer meet the standard diagnostic criteria for an acute episode (syndromal remission). Achieving symptomatic remission, defined as the presence of minimal symptoms, may take longer and an 2 additional months may be needed to attain the start of recovery, defined as a sustained remission. Time to remission is even longer following repeated recurrences of BD [6].

Moreover, BD can adversely affect the individual, reducing health-related quality of life and functioning, including employment and productivity at work [7]. It is becoming increasingly recognised that BD is associated with a higher level of functional impairment than previously thought, particularly with regard to social adjustment and vocational functioning [6,7].

In addition to patient burden, caregiver burden is currently one of the key factors in managing patients with BD. The term "caregiver burden" refers to the emotional, social, and financial stresses that caring for a relative or friend with mental illness imposes on the caregiver, and is defined as "the presence of problems, difficulties or adverse events which affect the life of psychiatric patient's caregivers" [8]. On the basis of the method established by Pollak and Perlik [9] the primary caregiver is defined as the family member, friend or significant other who satisfied the greatest number (and at least three) of five criteria, namely: a spouse, parent or spouse equivalent; has the most frequent contact with the patient; helps to support the patient financially; has been the most frequent collateral participant in the patient's treatment; and is the person contacted by treatment staff in case of emergency.

While caregivers can accept some of the burden for the care of patients with BD, management of the disease also places a substantial burden on healthcare providers. BD typically places greater demand on hospital psychiatric services than non-BD depression [10]. A study that permits comparison of different healthcare practices between countries may help to optimise resource utilisation.

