**Figure 1 F1:**
[figure not shown]
**Study design**.

The study comprises two different follow-up phases; one retrospective and one prospective (ambispective design). The retrospective phase for each patient started from the index event, which occurred a maximum of 12 months and minimum of 3 months before Time 0, and ended when the patient signed the informed consent form. Information from medical records related to the patient and their disease during that period (i.e. retrospective information - from index event to inclusion) was recorded in the electronic case report form (eCRF) at the inclusion visit. The prospective phase started when the first patient signed the informed consent form and will end when the last patient included in the study attends their final visit. Data for prospective analysis are collected as described at all visits (including the inclusion visit). All throughout the prospective phase, the required information will be recorded in the eCRF and the questionnaires completed every time the patient attends the psychiatrist's office (unless otherwise stated). The psychiatrist will schedule visits according to real-life clinical practice. No interventions, extra procedures, or extra visits will be required for the purpose of the study.

The study design means that patients will spend variable amounts of time in the study depending on the date of signing the informed consent form, the length of the enrolment period, and the date of their index episode. The minimum time in the study is 12 months and the maximum 27 months, considering the retrospective and prospective phases, and the 6 month enrolment period together (Figure 1).

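### Scale change starts at a first visit 3 to 18 months after index-event onset, in patients in mixed mood states, and the country mixed models adjust only for what is stated: age and gender

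*Protocol article*

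**What the plan says.** All references are to the protocol article.

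- **Outcome and models (Statistical analyses).** For the link between patient characteristics, management and "clinical outcome variables (clinical evolution, mood events, treatment-related events, suicide attempts, variation in scales), logistic and general linear models have been planned". No adjusters are listed for these models. A separate paragraph plans Cox and mixed models for between-country differences, with adjustment for age and gender. The section also says that analysis relative to the start of the mood event will be possible, because information is collected visit by visit from the index event.
- **Timing (Study design).** The retrospective phase starts from an index event that "occurred a maximum of 12 months and minimum of 3 months before Time 0, and ended when the patient signed the informed consent form". Total time takes in both phases and "the 6 month enrolment period together": "The minimum time in the study is 12 months and the maximum 27 months".
- **First rating (Measurements).** Table 2 notes: "First visit: the visit when the patient signs the informed consent form". CGI-BP, DAI-10, EQ-5D and FAST are listed for the prospective phase. Only the life chart and the Medication Possession Ratio are said to cover the retrospective phase as well.
- **State at entry (Patient population).** For an index event that began over 3 months ahead of Time 0, the section says that patients "were eligible even if the index event was not resolved, or if the index event had resolved and they subsequently initiated another event".
- **Course (Background).** Recovery from acute mania "may require 3-6 months and thus may no longer meet the standard diagnostic criteria for an acute episode". Symptomatic remission may come later, sustained remission later again, and both take longer after repeated recurrences.

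**The concern.** Change from a baseline means the same thing for everyone only if the baseline sits at a comparable point in the illness. Here it does not. One patient may be first rated three months into an unresolved episode, another a year after remission, and a third at the start of a new episode. The first has room to improve, the second can mainly stay level or worsen, and the third may improve whatever the management.

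The study aims to relate management patterns to clinical and functional outcomes and to compare countries. If one country's patients tend to be first rated earlier or in a worse state, that country will show more improvement on the scales without managing patients better. Age and gender carry no information on either feature.

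**Working it through.** **1. Lag from onset to first visit.** Inputs from Study design: index event to Time 0, 3 to 12 months; Time 0 to consent, 0 to 6 months.

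- Minimum: 3 + 0 = 3 months.
- Maximum: 12 + 6 = 18 months.

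**2. Check against the stated time in study.** 12 - 3 = 9 and 27 - 18 = 9, so the stated 12 and 27 months are reproduced if each patient has 9 prospective months. The 9 months is inferred, not stated. A common end at Time 0 + 15 months would give 3 + 15 = 18 to 12 + 15 = 27 months, which does not fit the stated minimum.

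**3. What exists at onset.** Life-chart mood and episode severity exist from the index event onward. The four scales do not. The remark on analysis relative to mood-event initiation therefore cannot supply an onset value for them. Later scores can still be modelled by time since onset, but the text calls this possible without tying it to a model.

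**4. Could the groups differ?** Sites and investigators says that patient profile may differ by type of site. Table 1 shows very different mixes: private practice is 65% in Austria and 10% in Ukraine, and public hospitals are 88% in Brazil. Visits follow routine practice, so the timing of the first visit may itself depend on how ill the patient is. A difference is foreseeable, but the documents do not show one.

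**5. Size, under assumptions that are not in the documents.** Assume that index date and enrolment date are uniform over their windows, that time to recovery is exponential with median m, and that follow-up is 9 months.

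- Mean lag: 7.5 + 3 = 10.5 months. Share of first visits within 6 months of onset: (3 × 3 / 2) / (9 × 6) = 8%. Within 8 months: (5 × 5 / 2) / 54 = 23%.
- Share still in the index episode at lag L: 0.5^(L/m).
- Share recovering in the next 9 months: 0.5^(L/m) - 0.5^((L+9)/m). For m = 6 and L = 3 this is 0.707 - 0.250 = 0.457.

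| Median recovery (months) | Still in index episode: L = 3 / L = 18 / average | Recover in next 9 months: L = 3 / L = 18 |
|---|---|---|
| 3 | 50% / 2% / 11% | 44% / 1% |
| 6 | 71% / 13% / 32% | 46% / 8% |
| 12 | 84% / 35% / 55% | 34% / 14% |

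**6. Lag or state?** A simulation scored each patient as in or out of an episode at the first visit and 9 months later, with 5% or 15% assumed to be in some other episode at each visit. Lag alone explained under 3% of the patient-level variance in change. State at the first visit explained about 24-65%. Starting state is the main driver, and lag is a weak proxy for it.

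**The case against.** The strongest case on the other side has five parts.

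- **The article condenses a fuller plan.** The covariates of the general linear models may be set out in a document that is not shown. The same sentence also counts functioning and quality-of-life status among the patient characteristics, without saying at which visit. This stands. A reader might infer that the management models ignore patient state, or that age and gender are their only adjusters. The text supports neither: age and gender belong to the between-country models.
- **Analysis by time since onset is foreseen.** This stands in part. It needs only the onset date and later scores, but it is a possibility, not a term in the stated country models.
- **Most patients may be past the index episode.** A reader might infer that scale change mostly measures natural recovery still to come. The documents do not support that. If the Background's 3-6 months is taken as a median, only 11-32% would on average still be in the index episode at the first visit. Treatment and new episodes also move the scores, recovery happens under treatment, and DAI-10 measures attitude to medication.
- **No imbalance is shown.** All countries share one eligibility window, with systematic invitation or simple random selection. This stands as to size. It does not remove the possibility, because the article itself expects patient profiles to differ by site type.
- **Adjustment has a price.** State and score at consent may partly result from 3 to 18 months of the management under study, so adjusting for them can remove part of the association sought. This stands and shapes the fix.

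**Conclusion.** The point holds as a risk of confounding in a stated model. Two facts follow directly from the text: scale change can start only at a first visit 3 to 18 months after onset, in patients whose mood state is mixed by design; and the country mixed models are stated with adjusters that reflect neither. The extent of any bias is unknown, because it depends on how lag and starting state differ between countries, which the documents do not report. The recovery shares above show only that the effect could matter at the extremes of lag. They rest on uniform timing, exponential recovery and an inferred 9 months of follow-up.

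The consequence is limited to the scale outcomes. The sample size is built on the proportion with episodes, and the life chart follows mood from the index event onward. The change is worth making, but the point does not undermine the study as a whole.

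**What to change.** In Statistical analyses:

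1. State that change in CGI-BP, DAI-10, EQ-5D and FAST is measured from the first visit, and that analysis relative to mood-event initiation has no onset value for these scales.
2. In the country mixed models of scales, add months from index-event onset to first visit, and life-chart mood state at first visit (in an episode or not, and polarity). Where the outcome is change from the first visit, add the first-visit score too.
3. Show change separately for patients in and out of an episode at the first visit.
4. Apply the same to the management models of scale change, unless the full plan already does so.
5. Report these results beside the age- and gender-adjusted ones. Where the two differ, say that first-visit state and score may partly reflect earlier management.

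The cost is a few sentences, some extra model terms and a second set of estimates. Onset date, consent date and life-chart mood are already recorded, so no new data are needed.
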